## Abstract

**Background:**

Critically ill patients are at risk of developing a postintensive care syndrome (PICS), which is characterized by physical, psychological, and cognitive impairments and which dramatically impacts the patient’s quality of life (QoL). No intervention has been shown to improve QoL. We hypothesized that a medical, psychological, and social follow-up would improve QoL by mitigating the PICS.

**Objective:**

This multicenter, randomized controlled trial (SUIVI-REA) aims to compare a multidisciplinary follow-up with a standard postintensive care unit (ICU) follow-up.

**Methods:**

Patients were randomized to the control or intervention arm. In the intervention arm, multidisciplinary follow-up involved medical, psychological, and social evaluation at ICU discharge and at 3, 6, and 12 months thereafter. In the placebo group, patients were seen only at 12 months by the multidisciplinary team. Baseline characteristics at ICU discharge were collected for all patients. The primary outcome was QoL at 1 year, assessed using the Euro Quality of Life-5 dimensions (EQ5D). Secondary outcomes were mortality, cognitive, psychological, and functional status; social and professional reintegration; and the rate of rehospitalization and outpatient consultations at 1 year.

**Results:**

The study was funded by the Ministry of Health in June 2010. It was approved by the Ethics Committee on July 8, 2011. The first and last patient were randomized on December 20, 2012, and September 1, 2017, respectively. A total of 546 patients were enrolled across 11 ICUs. At present, data management is ongoing, and all parties involved in the trial remain blinded.

**Conclusions:**

The SUVI-REA multicenter randomized controlled trial aims to assess whether a post-ICU multidisciplinary follow-up improves QoL at 1 year.

**Trial Registration:**

Clinicaltrials.gov NCT01796509; https://clinicaltrials.gov/ct2/show/NCT01796509

**International Registered Report Identifier (IRRID):**

DERR1-10.2196/30496

## Introduction

### Background and Rationale

In the last 2 decades, mortality has significantly decreased in the intensive care unit (ICU) [1]. However, the mortality rate at 1 year after ICU discharge remains high, ranging from 10% to 30%, according to age and severity of critical illness [2-5]. In addition, ICU survivors often develop physical, psychological, and cognitive impairments, which have been grouped under the term postintensive care syndrome (PICS) [6,7]. The incidence of post-ICU complications depends on various factors, including the patient’s pre-existing medical history, age, critical illness severity, as well as ICU and post-ICU care [8]. Because PICS is a dynamic process, its incidence changes according to the time of its assessment after ICU discharge. Physical disabilities are reported in about 14%-39% of patients at 1 year after ICU discharge and are mainly related to an ICU-acquired weakness [3,9-13]. Post-ICU psychological disorders include anxiety, depression, and posttraumatic stress syndrome (PTSD), which can affect from one-fifth to two-thirds of patients [3,14-18]. They result in an increased risk of suicide [19]. Concerning cognitive functions, 30%-90% of patients will complain of impaired memory, attention, concentration, and speech fluency [8,20-23]. They are more frequent in patients with pre-existing cognitive dysfunction and among those who have severe critical illness or who have developed delirium during their ICU stay [22]. PICS has a dramatic impact on a patient’s post-ICU trajectory, with an increased rate of mortality and rehospitalization and decreased return to home and work; it therefore profoundly affects a patient’s quality of life (QoL) [7]. Indeed, 6-month to 1-year post-ICU mortality ranges from 10% to 45%, according to age and severity and cause of critical illness [3,4,24-26]. Nearly 5%-10% of patients are readmitted to an ICU within the first year after their ICU discharge [4,27,28]. The 6-month to 1-year post-ICU QoL is significantly lower than age and sex-matched populations, with an impairment of physical, mental, and social domains [24,25,29]. QoL has been reported as being reduced by 29%-63% [30,31].

Because of its medical, social, and economic burden, PICS has been identified by the community of ICU physicians as a research priority [7]. There have been randomized controlled trials (RCTs) on post-ICU interventions, but the type of intervention, endpoints, time frame, and populations have varied.

Briefly, a rehabilitation program has been shown to improve physical [32] and psychological [4] status and increase patient satisfaction, but it has not ameliorated health-related QoL (HRQoL) [33]. A systematic review of RCTs indicated that post-ICU follow-up models focusing on psychological or medical management interventions were associated with fewer PTSD symptoms [34]. RCTs on care coordination have shown that neither a nurse-led post-ICU program in critically ill patients nor primary care physician–led follow-up in patients with sepsis was beneficial [24,35].

At the time of the design of our RCT (ie, 2010), there were a limited number of RCTs that focused on the benefit of post-ICU care coordination, but none integrated a social follow-up. Because of the interdependency of its domains, we hypothesized that a medical, psychological, and social follow-up would be more appropriate for mitigating PICS. We carried out a multicenter RCT to determine whether a post-ICU multidisciplinary follow-up would improve QoL at 1 year and would then also improve physical, psychological, cognitive, and social status and reduce mortality and medical requirements (ie, hospitalization, outpatient consultations).

### Objectives

The primary objective is to assess the impact of medical, psychological, and social follow-up on death and HRQoL at 1 year after discharge from ICU.

The secondary objectives are to assess the benefit of a post-ICU follow-up on muscle strength, functional capacities, cognitive abilities, and psychological state, as well as on social and professional reintegration.

### Trial Design

The SUIVI-REA trial is an open multicenter parallel group RCT comparing a program of medical, psychological, and social follow-up with standard care in patients 1 year after ICU discharge.

## Methods

### Study Setting

A total of 11 centers, including 9 general hospitals and 2 university hospitals, participated in this study. Factors determining center participation were a capacity to include patients, and the availability and willingness of psychologists, social workers, and physicians to implement post-ICU consultations. All participating centers had previously participated in clinical trials. Training on study procedures was provided to all participating staff members. Documents required for the study, including the study protocol and management guidelines, were available in each participating ICU.

### Eligibility Criteria

Adult patients were eligible if they (1) lived in an area near the participating center; (2) had required mechanical ventilation (MV) for more than 3 days; (3) had a life expectancy greater than 1 year (defined by a McCabe score <2 and the absence of metastatic cancer); (4) were enrolled with a general practitioner; (5) were affiliated to the social health care system; and (6) had given their written informed consent. Duration of MV of at least three days was selected for patients with severe critical illness. A general practitioner was mandatory because we believe he/she should be involved in the post-ICU follow-up program. Proximity to a participating hospital was to facilitate attendance at post-ICU consultations.

Patients were excluded from the trial if they (1) had been hospitalized in an ICU in the previous year; (2) were followed for a pre-existing chronic myopathy; (3) had been admitted for serious burns, severe brain injury, suicide, or self-induced poisoning; (4) had a psychiatric disorder or dementia; (5) were under guardianship; (5) did not speak fluent French; (6) were homeless; and (7) were pregnant. These criteria were established to exclude those not benefiting from a specific follow-up and those who were unable to give their consent or to follow the post-ICU program. Patients with chronic myopathy were excluded because 1 participating center already had in place an organized, specific long-term multimodal follow-up for this condition.

All patients from one of the participating ICUs were screened for eligibility by ICU physicians before hospital discharge. The reasons for nonrandomization were collected.

### Informed Consent

Written informed patient consent had to be obtained by the investigator of the participating center. A copy of the consent form was given to every patient, with the investigator retaining a copy.

As observational studies have shown that patients with delirium were at risk of developing psycho-cognitive disorders [36], we decided to remove impairment of consciousness as an exclusion criterion because a post-ICU follow-up would be beneficial for these patients. In case of impaired consciousness (ie, delirium), the investigator sought written consent from the next of kin. As soon as the patient’s status allowed, written informed consent for the continuation of the research and analyses of the data was obtained. There was no additional consent for ancillary studies.

### Interventions

#### Explanation for the Choice of Comparators

At the time of the trial design, there was no recommendation for post-ICU follow-up, in terms of both type and rate of consultations. Therefore, the comparator did not differ from the current practice and “no post-ICU follow-up” was used to control the intervention.

#### Intervention Description

Patients were included at time of their discharge from the ICU either to home or to another department of the same or another hospital. By convention, day 1 corresponded to the date of inclusion. The randomization was performed after the baseline assessment at the time of inclusion. The last consultation was planned at 12 months, after the simple blinded collection of the primary endpoint.

In both therapeutic groups, patients’ medical, psychological, and social scores and questionnaires were assessed at the time of inclusion and at 12 months, to evaluate whether the characteristics of the 2 therapeutic groups were comparable at baseline and to determine the respective course of post-ICU discharge impairments in both groups. The scores and questionnaires were completed by the patient alone or with the help of the research assistant. If the patient was included in the control group, the test results were sealed for disclosure at the end of the study. Test results for intervention group patients were passed to the multidisciplinary team to avoid repeating the tests.

The patients from the control group had no additional post-ICU consultation. In the intervention group, patients received a multidisciplinary consultation within the first weeks after inclusion, at 3 months, and (if necessary) at 6 months. This was a consultation with a physician, a psychologist, and a social worker. Both the physician and social worker were from the ICU participating in the trial. The ICU-referring psychologist was active in 9 centers. A psychologist was specifically recruited for performing the follow-up in the remaining 2 centers. The same multidisciplinary team was used for follow-up in each patient.

The ICU physician consultation comprised (1) the collection of information about the current treatment, weight, vital signs, comorbidities, and symptoms; (2) the date and cause of readmission at the hospital; (3) standardized general examination; (4) functional status using the Medical Research Council (MRC) sum score for assessing muscle strength and the Barthel index and Instrumental Activities of Daily Living (IADL) scores for assessing disability; and (5) cognitive status using the Minimal Mental State (MMS) scoring system. It was recommended that the participant was followed by the same ICU physician throughout follow-up. The ICU physician could prescribe a paraclinical exploration or a treatment, but it was recommended that they referred to the patient’s general practitioner, except in the case of an emergency.

The consultation with the psychologist consisted of the collection of the Hospital Anxiety and Depression Scale (HADS) and Impact Event Scale-Revised (IES-R) scores for assessing PTSD as well as an interview during which the participant reported any psychological difficulties. The consultation with the social worker consisted of the collection of the social questionnaire response and an interview during which the patient reported about their QoL (Euro Quality of Life-5 dimensions [EQ5D]), social and professional difficulties, and needs.

In total, the medical, psychological, and social consultations took 2 h and 30 min. They were followed by a meeting between the ICU physician, psychologist, and social worker to discuss the participant’s status and requirements and to write a summary report to forward to the general practitioner.

### Criteria for Discontinuing or Modifying Allocated Interventions

Any participant could discontinue participation in the research at any time for any reason. The investigator could temporarily or permanently discontinue one’s participation in the research for any reason that affected the participant’s safety or was in the best interests of the participant. In the event of premature termination of the research, or withdrawal of consent, data collected prior to the premature termination could be used. The reasons for discontinuing participation in the research were to be registered in the participant’s file.

### Strategies to Improve Adherence to Interventions

The participating teams were informed monthly of the course of the study and reminded of the main elements of the trial. The research technician at each center organized consultations for intervention patients at 3, 6 (if needed), and 12 months. Patients were reminded of these consultations 15 days beforehand. Control patients were called at least once by the research technician to remind them of their 12-month consultation, which was planned at time of their ICU discharge.

### Relevant Concomitant Care Permitted or Prohibited During the Trial

For deontological reasons, the patients of both groups continued to be followed by their general practitioner or specialist physician, but they were allowed to see a new physician, a physiotherapist, or psychologist. The purpose of the trial was to determine whether a post-ICU follow-up improved standard patient care.

### Provisions for Posttrial Care

In France, the research sponsor insurance offers a subsequent period of insurance 10 years from the end of the research. Consequently, in the event of poststudy damage to participants related to their participation in the research, the complaint would be admissible whenever it occurred during this period.

### Outcomes

The primary outcome was QoL at 12 months. The QoL was assessed using the EQ5D and by telephone by a blinded investigator. The patient was asked not to disclose to which group they were randomized. The EQ5D is a standardized self-completed instrument for measuring generic HRQoL. The Euro Quality of Life-5 dimensions-5 Levels (EQ5D-5L) comprises 5 dimensions: mobility, self-care, usual activities, pain/discomfort, and anxiety/depression. Each dimension has 5 problem levels: none, slight, moderate, severe, and extreme. Finally, the weighted sum of the responses obtained provides a cardinal measure (between 0 for death and 100 for the total absence of a problem), which is also suitable for medicoeconomic evaluation [37]. The EQ5D has been used in various post-ICU follow-up studies [30,35,38-41]. The secondary outcomes were mortality, cognitive, psychological, and functional status; social and professional reintegration at 1 year; as well as the rate of rehospitalization and outpatient consultations within the first year (Table 1).

**Table 1 table1:** Research timeline for each participant.

Timepoint	Inclusion	ICU^a^ discharge	3 months	6 months	12 months
Consent collection	Both groups				
Pursue consent collection		Both groups	Both groups	Both groups	
Demographics, medical history, critical illness, and ICU stay characteristics	Both groups				
Collection of clinical data	Both groups	Follow-up group	Follow-up	Follow-up	Both groups
Standard biological tests	Both groups		group	group	Both groups
Adverse events		Follow-up group	Follow-up	Follow-up	Both groups
Final assessment of main outcome					Both groups
Final assessment of secondary outcomes					Both groups

^a^ICU: intensive care unit.

### Sample Size

At the time of the study design, other studies indicated that 10% of patients discharged from ICU died within the first year and 40% had a moderate to severe impairment on at least one dimension of the EQ5D [32,41].

Therefore, we estimated that at least 50% had a very poor outcome, combining death and severe to extreme impairment of at least one EQ5D dimension. [23]. The study was then powered to detect a decrease from 50% to 37% of patients with very unfavorable outcome with a power of 80% and a 2-sided 5% alpha risk, assuming this rate would be 50% in the control arm. Accordingly, the sample size was 249 patients per group. We anticipated that 20% of the patients would be lost to follow-up, so the sample size was increased to 300 per arm. The study therefore initially planned to enroll a maximal sample size of 600 patients. However, as the rate of loss to follow-up has, indeed, proved to be 10%, we decided to decrease the sample size to 520 patients. Finally, 546 patients were included. Interestingly, recent studies on comparable populations of critically ill patients showed that there was a 1-year mortality rate of between 10% and 28% [2,3,5,8,20] and that about 60% of patients had a moderate to severe impairment on at least one dimension of the EQ5D [3,10,29]. These findings suggest that our original estimation is still appropriate.

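### The 50% control rate is built from moderate-to-severe impairment, but the primary event counts only severe-to-extreme, so the stated 80% power is unsupported for the endpoint analysed

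*Protocol article*

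**What the plan says.** The Sample Size section of the protocol article starts from earlier studies in which 10% of patients discharged from ICU died within a year and "40% had a moderate to severe impairment on at least one dimension of the EQ5D". The next sentence draws a conclusion from this: "we estimated that at least 50% had a very poor outcome, combining death and severe to extreme impairment", where the impairment may be on any one EQ5D dimension or more. The trial was then "powered to detect a decrease from 50% to 37% of patients with very unfavorable outcome". The design values are 80% power and a two-sided significance level of 5%, and the control rate is fixed by "assuming this rate would be 50% in the control arm". This gave 249 patients per group.

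The section later defends the assumption with newer data: 1-year mortality of 10% to 28%, and "about 60% of patients had a moderate to severe impairment on at least one dimension of the EQ5D". It concludes: "These findings suggest that our original estimation is still appropriate".

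The Outcomes section describes the instrument: "Each dimension has 5 problem levels: none, slight, moderate, severe, and extreme". Under Statistical Methods for Primary and Secondary Outcomes, the main endpoint is death or a severe-to-extreme level in one of the five dimensions.

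**The concern.** The evidence and the endpoint use different thresholds. The evidence counts patients from the moderate level upward, while the endpoint counts survivors only from severe upward. On the trial's own scale, a patient whose worst dimension is moderate belongs to the 40% but is not an event. Adding 10% and 40% therefore gives the rate of a broader composite, yet the text carries it over as the rate of the primary event.

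The control rate is the main input to the sample size. If it is not the rate of the event analysed, then 249 per group and 80% power describe a different trial. The article also lists among its strengths that the trial was designed and powered for this question. A reader of a null result would rely on that statement when judging whether a worthwhile benefit had been ruled out.

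**Working it through.** **1. Reproduce the plan's figure.** Inputs from Sample Size: p1 = 0.50, p2 = 0.37, two-sided alpha 0.05 (z = 1.960), power 80% (z = 0.842), equal arms. The mean rate is 0.435.

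- n = [1.960 × √(2 × 0.435 × 0.565) + 0.842 × √(0.50 × 0.50 + 0.37 × 0.63)]² / 0.13² = 228 per group after rounding up.
- With continuity correction: 243 per group.

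The stated 249 is within 3% of 243. The step from 50% versus 37% to the sample size is sound; the problem lies in the 50%.

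**2. Trace the 50%.**

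| Quantity | Impairment levels counted | Figure in the document |
|---|---|---|
| Source evidence | moderate to severe | 40%, plus 10% deaths |
| Primary event | severe to extreme | none given; 50% asserted for death and impairment together |
| Later check | moderate to severe | about 60%, plus 10–28% deaths |

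10% + 40% = 50% matches the assumed rate exactly, but for the composite in the first row.

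**3. Denominator.** If the 40% is a share of all discharged patients, the sum is right, because death and impairment in survivors cannot overlap. If it is a share of survivors, the broader composite is 0.10 + 0.90 × 0.40 = 0.46. The text does not settle which applies.

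**4. The later check.** If the 60% is among survivors, the broader composite is 0.10 + 0.90 × 0.60 = 0.64 up to 0.28 + 0.72 × 0.60 = 0.71. If simply added, it is 0.70 to 0.88. Either way these are moderate-to-severe rates and give no figure for severe-to-extreme.

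**5. Consequence for power.** The document gives no severe-to-extreme rate, so control rates of 50%, 40% and 30% are assumed. The test is a two-proportion z-test (pooled variance under the null, no continuity correction): power = Φ[(d − 1.960 × SE0) / SE1]. Here d is the difference, SE0 = √(2 × p̄(1 − p̄)/n) and SE1 = √([p1(1 − p1) + p2(1 − p2)]/n). With the 10% loss to follow-up given in Sample Size, 546 × 0.9 / 2 = 245.7, taken as 245 per arm.

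Example, control rate 30% with relative risk 0.37/0.50 = 0.74 held: p2 = 0.222, d = 0.078, SE0 = 0.0397, SE1 = 0.0395. The numerator is close to zero, so power is 50%.

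| Effect held constant | n per arm | Control 50% | Control 40% | Control 30% |
|---|---|---|---|---|
| Relative risk 0.74 | 245 | 83% | 68% | 50% |
| Odds ratio (0.37/0.63)/(0.50/0.50) = 0.587 | 245 | 83% | 79% | 72% |
| Difference of 13 points | 245 | 83% | 86% | 93% |
| Relative risk 0.74 | 273 | 87% | 72% | 55% |

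The last row uses all 546 patients (546/2 = 273), because the Results section says every randomized patient completed follow-up for the primary outcome. Holding 13 points at a 30% control rate means a relative reduction of 0.13/0.30 = 43%, against the planned 0.13/0.50 = 26%.

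**The case against.** Three defences deserve weight.

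*The sum and the newer figures.* A reader might infer that adding 10% and 40% is an arithmetic error, or that the newer figures contradict 50%. The documents support neither. As worded, both percentages can share the denominator of patients discharged from ICU, and then the sum is correct; 46% is only a possibility. The estimate is stated as a lower bound, so higher rates for a broader category do not contradict it. With mortality of 10% to 28%, a 50% event rate needs (0.50 − 0.10)/0.90 = 44% down to (0.50 − 0.28)/0.72 = 31% of survivors at severe or extreme, which fits inside 60%. What stands is that the newer figures do not demonstrate the claim.

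*Unseen sources.* Reference 23 is attached to the 50% sentence and might hold a suitable rate, and the cited studies may have used other level labels. But no severe-to-extreme figure is quoted, no mapping between labels is given, and the wording derives the 50% from the 10% and 40%.

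*Underpowering.* It is tempting to conclude that the trial is underpowered. That requires holding the relative risk, and the plan states only the two rates, not which effect measure stays constant. With 13 points held, power rises as the control rate falls. The direction is therefore open, although nothing in the document justifies the larger relative effect that this case needs.

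**Conclusion.** The concern holds in this form: the 50% control rate belongs to death or moderate-to-severe impairment, while the primary event is death or severe-to-extreme impairment. The 80% power is therefore unsupported for the endpoint analysed, and the later check does not repair it. This rests on the article's own wording and scale.

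The size rests on assumed control rates. Between 50% and 30%, with 245 per arm, power runs from 83% down to 50% or up to 93%, depending on the effect scale. These powers come from an unadjusted two-proportion test. The planned analysis is an adjusted piecewise exponential model, so they are a yardstick and not the exact power of that analysis.

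This should be fixed but does not threaten the trial's conduct. Recruitment closed in 2017, and the correction changes neither the sample size, the endpoint nor the analysis. It changes what may be claimed about power when the result is read.

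**What to change.** Before unblinding:

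1. Restate the assumed control rate for death or severe-to-extreme impairment, with its source, and say whether the impairment figure refers to all discharged patients or to survivors. If to survivors, combine it as d + (1 − d) × q, where d is mortality and q the impairment rate among survivors.
2. Replace the single 80% with a short table of power or detectable difference over a range of control rates, on a named effect scale, for the 546 enrolled.
3. Delete the sentence saying that the newer findings support the original estimate.
4. Optionally, report the pooled event rate, blinded to arm, with the detectable difference it implies.

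The cost is a few sentences and one small table. Item 4 would be an extra step, since the article describes data verification and audits but no monitoring of pooled event rates. The drawback is that the stated power may become less favourable.

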### Assignment of Interventions: Allocation

#### Sequence Generation

The randomization list, generated by an independent statistician, was balanced between arms. Randomization was stratified by center using a permuted block of unrevealed size randomization. As critical severity could potentially impact the rate and intensity of psychological, cognitive, and physical impairment, stratification was made on this basis.

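### The loss-to-follow-up arithmetic is wrong: 520 patients at 10% loss leave 234 evaluable per arm, not the 249 required, and 300 per arm at 20% loss leave 240

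*Protocol article*

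**What the plan says.** All the figures are in the Sample Size section of the protocol article.

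- **Design target:** the trial was "powered to detect a decrease from 50% to 37% of patients with very unfavorable outcome", at 80% power and a two-sided alpha of 5%.
- **Requirement:** "Accordingly, the sample size was 249 patients per group".
- **First inflation:** "We anticipated that 20% of the patients would be lost to follow-up, so the sample size was increased to 300 per arm", giving a maximum of 600.
- **Reduction:** observed loss is put at 10%, and for that reason "we decided to decrease the sample size to 520 patients".
- **Outcome:** "Finally, 546 patients were included". Table 2 under Recruitment also gives 546 as the number to include.

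Allocation is equal: "The randomization list, generated by an independent statistician, was balanced between arms".

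Two other sections bear on the loss rate. Results reports that every randomized patient completed follow-up for the primary outcome. The section on nonadherence and missing data expects no missing data, yet plans maximum-bias imputation for the primary outcome.

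**The concern.** The text raises 249 to 300 because of expected loss, so 249 is the number that must be evaluable after loss. To keep n patients after a fraction L is lost, n/(1 − L) must be enrolled. The step to 300 looks like n × (1 + L), which falls short. The step to 520 is a reduction made during the trial, with the lower loss rate as its only stated reason, and that rate does not lead to 520.

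What is at stake is whether the published justification for reducing the sample supports the number adopted. An unexplained cut below the plan's own requirement invites challenge, particularly if the result is null.

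**Working it through.** **Inputs** (Sample Size, with equal allocation from Sequence Generation): p1 = 0.50, p2 = 0.37, difference d = 0.13, two-sided alpha 0.05, power 80%; 249 per arm required; loss 20% then 10%; totals 600, 520 and 546.

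**Step 1. Reproduce 249.** With mean rate 0.435, the pooled formula is

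n' = [1.960 × √(2 × 0.435 × 0.565) + 0.842 × √(0.50 × 0.50 + 0.37 × 0.63)]² / 0.13² = 227.1, so 228 per arm.

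The unpooled formula gives 225 and the arcsine formula 227. With continuity correction,

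n = (n'/4) × [1 + √(1 + 4/(n' × d))]² = 242.2, so 243 per arm.

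The corrected value is the closest, within 3% of 249. The article does not name the test.

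**Step 2. Inflation for 20% loss.**

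- Multiplication: 249 × 1.2 = 298.8, which matches 300.
- Division: 249/0.8 = 311.25, so 312 per arm (624 in total).
- Evaluable from 300 per arm: 300 × 0.8 = 240, which is 9 short.

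**Step 3. Revision for 10% loss.**

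- Division: 249/0.9 = 276.7, so 277 per arm (554 in total).
- Multiplication: 249 × 1.1 = 273.9, so 274 per arm (548 in total).
- Evaluable from 520: 260 × 0.9 = 234 per arm, which is 15 short (15/249 = 6.0%).
- Evaluable from 546: 273 × 0.9 = 245.7 per arm, which is 3.3 short (1.3%).

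Neither rule gives 520. Multiplying instead of dividing accounts for 554 − 548 = 6 of the 34 patients between 520 and 554. A total of 520 leaves 249 per arm only if loss is at most 1 − 249/260 = 4.2%; for 546 the limit is 1 − 249/273 = 8.8%.

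**Step 4. Power for 50% versus 37%.** The corrected column puts (n − 1/d)²/n in place of n, which inverts the correction in Step 1.

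| Total | Loss | Evaluable per arm | Uncorrected | Continuity-corrected |
|---|---|---|---|---|
| 498 | 0% | 249 | 83.5% | 81.1% |
| 600 | 20% | 240 | 82.1% | 79.6% |
| 520 | 10% | 234 | 81.2% | 78.5% |
| 546 | 10% | 245.7 | 83.0% | 80.6% |
| 520 | 0% | 260 | 85.1% | 82.9% |
| 546 | 0% | 273 | 86.7% | 84.8% |

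**The case against.** The strongest reply is that nothing of substance was lost. The target of 520 was passed, and 546 at 10% loss still gives at least 80% power on either basis. The figure of 249 is itself slightly generous, at 81.1% to 83.5% power. On the uncorrected formula, which needs only 228, even 234 per arm is enough. If Results is right that primary-outcome follow-up was complete, 546 gives 273 per arm, well above 249. All of this stands as far as consequences go. It does not rescue the derivation: the uncorrected formula cannot be the source of 249, and complete follow-up contradicts the 10% loss that is the only reason given for the cut.

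The imputation plan is not a rescue either. Assume 10% missing in each arm, unrelated to outcome. Counting missing controls as successes and missing intervention patients as failures turns 50% versus 37% into 0.9 × 50% = 45% versus 0.9 × 37% + 10% = 43.3%. Imputed patients therefore cannot simply be counted towards the 249.

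A reader might infer four stronger claims, and the document supports none of them:

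- **That multiplying instead of dividing produced 520.** It explains 300, but at 10% it gives 548. The origin of 520 is not stated.
- **That 249 evaluable per arm was reached at no stage.** This is true only under the loss rates in Sample Size; under the Results statement it is false.
- **That the trial as enrolled is underpowered.** At 546 the shortfall is 1.3% and power is at least 80.6%.
- **That the article asserts that 520 suffices or that 80% power was preserved.** It says neither. Its closing remark that the original estimation still applies concerns mortality and impairment rates.

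**Conclusion.** The point holds as an error in the stated figures. Taking 249 as the evaluable requirement and the article's own loss rates, 300 per arm is 9 short at 20% loss and 520 in total is 15 per arm (6%) short at 10% loss. No standard inflation of 249 gives 520.

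The effect on power is small. Only 520, and marginally 600 at 20% loss, drop below 80%, and only on the continuity-corrected basis: by 1.5 points for 520 and 0.4 points for 600. The enrolled 546 stays above 80% on both bases. These power figures assume a simple comparison of two proportions at 50% and 37%, with loss equal in the two arms and unrelated to outcome.

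The evaluable number at 546 cannot be settled from the article, because Sample Size and Results disagree about loss.

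**What to change.** Revise the text of the sample-size justification, ideally before the database freeze, which Results describes as still to come:

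1. Name the test and any continuity correction behind 249.
2. Restate the inflation as n/(1 − loss): 312 per arm at 20% and 277 per arm at 10%.
3. State that 520 does not leave 249 evaluable per arm at 10% loss, or give the actual basis for 520.
4. Reconcile the 10% loss in Sample Size with the complete primary-outcome follow-up in Results. If the two refer to different things, such as attendance at consultations and the telephone EQ5D, say so.
5. Only then report evaluable numbers and power at 546: about 246 per arm and 80.6% to 83.0% if loss was 10%, or 273 per arm and 84.8% to 86.7% if there was none.

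The cost is wording only. No further enrolment and no change to the analysis is needed; the figures at the stated loss rates become slightly less favourable.
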